### Statistical analysis

Categorical data is expressed as number and rate, while continuous data is expressed as means ± standard deviation if they are normally distributed or median with interquartile range otherwise. Student’s *t*-test or Mann-Whitney *U*-test is used for univariate analysis of continuous data. χ^2^-test or Fisher’s exact test is used for categorical data. For primary analyses, multivariate logistic regression is used to calculate adjusted odds ratio and 95% confidence interval for short-term outcomes. Cox proportional hazard regression analysis and marginal structural model are adopted to assess the association between limb configuration and time-to-event outcomes.

The propensity score to undergo CL or SL is estimated by logistic regression model based on demographic and anatomic information. Inverse probability of treatment weighting adjusted analyses are performed to achieve weighted balance with standardized differences < 0.10. Sensitivity analysis is conducted to stabilize the weights by truncating the non-overlapping tails of the propensity score distributions which below or above the 1st and 99th percentiles. Subgroup analysis is conducted in terms of large aneurysm sac, severely angulated neck, tortuous iliac arteries and iliac landing zone (whether using bell-bottom iliac stent graft). In addition, this analysis will be carried out in AP and LR subgroups. R studio Version 1.2.1335^1^ and Empower (X&Y solutions, Inc., Boston, MA)^2^ are utilized for statistical analysis.

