### Allocations of intervention

Based on the anatomic features of the aneurysm by intraoperative imaging, surgeons will determine whether to adopt CL or SL configuration. When both configurations are feasible, surgeons will assign the limb configuration based on covariate adaptive matching between the two groups. The major matched covariates are as follows: age, gender and aneurysm diameter. Both surgeons and participants are not blinded to the interventions, and only statisticians who analyze the data are blinded.

The CL and SL configurations are defined as crossed or uncrossed limb grafts in anteroposterior view of the final angiogram, respectively. CL is further subdivided into anterior-posterior (AP) cross and left-right (LR) cross, which correspond to ≥ 50 and < 50% overlapped areas between two limb grafts in the angiogram. SL is similarly subdivided into AP parallel and LR parallel with the same definition.

The included patients will receive the same perioperative management, including blood pressure control, analgesia and medication with antiplatelets and statins. In interventional operating room, both common femoral arteries will be used for percutaneous or cut down access. After administration of 0.5 mg/kg unfractionated heparin, graft stents are placed in accordance with instruction for use by an experienced surgeon of vascular surgery. Treatment procedures are performed under a standard protocol. The Endurant II or IIs Stent Graft (Medtronic, Minneapolis, Minn) is used for repair.

Postoperative medications include antiplatelet monotherapy (aspirin 100 mg once a day or clopidogrel 75 mg once a day) and statins. Patients are expected to take these medications all life unless severe adverse event occurs. Anticoagulants, such as low molecular weight heparin or direct oral anticoagulants, will be used according to surgeons’ decision.

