### Data collection

Figure 1 shows the flow diagram of the trial. Once patients are admitted, baseline data will be collected for both groups, including demographic characteristics, comorbidities and anatomical variables. The demographics are collected from history taking and hospital information system. The comorbidity is evaluated by the Charlson Comorbidity Index to quantify its severity. Anatomical variables are as follows: length of aneurysm neck, oversizing ratio in proximal neck and distal limb, neck angulation, maximum diameter of aneurysm sac, intramural thrombus load of aneurysmal sac, iliac tortuosity, common iliac artery aneurysm and distal iliac calcification. We will report reasons for withdrawal for each group and compare the reasons qualitatively. Details of the procedure, consisting of operation time, radiation exposure time and contrast medium dosage, are recorded immediately after the operations. At preoperative and postoperative evaluation (24, 48, and 72 h), laboratory examinations will be conducted and corresponding results will be collected from the laboratory information system.

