**FIGURE 3 F3:**
[figure not shown]
Illustrations for abdominal aortic aneurysm with hostile anatomy. **(A)** Aneurysm with “normal” appearance; **(B)** aneurysm with angulated neck and tortuous iliac arteries.

Described by Ramaiah et al. in 2002 first (15), CL technique (Figure 4) is a useful adjunct to solve this problem by connecting ipsilateral guidewire to contralateral gate, arranging the limb graft just like a ballerina. It is expected to facilitate the procedure and, furthermore, reduce graft gate disconnection and endoleak. The true effect of CL, however, on postoperative outcomes has yet to be elucidated and currently no indications or contraindications have been described. This is a challenging issue for research because involved patients are always characterized by complicated anatomical conditions, which could induce considerable selection bias. Additionally, randomized controlled trials, with the highest evidence level, could be extremely difficult to conduct, as the performance of CL or SL is mainly based on anatomy and surgeons’ experience. Related studies, mainly cohort studies, have made inconsistent conclusions on this issue. Several studies revealed no difference in perioperative death, short or long term endoleak, limb graft occlusion, aneurysm sac expansion, reintervention or overall survival (19, 20), which was confirmed by a recent meta-analysis (21). While in our previous cohort study, which was characterized by the largest sample size and additional subgroup analysis, patients with large aneurysm sac and tortuous iliac arteries encountered fewer type I endoleaks in the CL group (22). This conclusion was consistent with a recent hemodynamic study revealing that this non-standard configuration could sustain higher wall shear stress and helicity characteristics (16, 17). However, it was questioned that it may be modified delivering system, instead of CL, that improved prognosis (36). Moreover, other computational analyses did not conclude likewise. Georgakarakos et al. revealed that the displacement force, one of the targets that CL aims at, was only slightly affected by the CL configuration and this effect could be blunted by concomitant modifications of the stent (37). Qing et al. studied the hemodynamic performance of these two configurations and concluded that the main factor affecting the index was the angle of aneurysm neck, while configuration had little effect on hemodynamics (18).

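### Surgeons' experience is named as a main driver of crossed versus standard limb choice, but the propensity score uses only demographic and anatomic information, so operator experience may confound the weighted comparison

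*Protocol article*

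**What the plan says.** All references are to the Protocol article.

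- **Who chooses (Allocations of intervention).** Guided by aneurysm anatomy on intraoperative imaging, "surgeons will determine whether to adopt CL or SL configuration". Where either configuration would work, surgeons assign it by covariate adaptive matching: "The major matched covariates are as follows: age, gender and aneurysm diameter".
- **Who operates (same section).** The text says "graft stents are placed in accordance with instruction for use by an experienced surgeon of vascular surgery". It gives no number of operators, case volume or CL experience.
- **What drives the choice (Discussion).** Randomized trials are described as very hard to conduct, "as the performance of CL or SL is mainly based on anatomy and surgeons’ experience".
- **What is recorded (Data collection).** On admission, "baseline data will be collected for both groups, including demographic characteristics, comorbidities and anatomical variables". For the operation itself: "Details of the procedure, consisting of operation time, radiation exposure time and contrast medium dosage, are recorded immediately after the operations". The operator is not named in either list.
- **What is adjusted for (Statistical analysis).** "The propensity score to undergo CL or SL is estimated by logistic regression model based on demographic and anatomic information". Weighting then aims for standardized differences below 0.10. The subgroups concern sac size, neck angulation, iliac tortuosity, landing zone and the spatial type of crossing. None concerns the operator.

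**The concern.** A propensity score models why a patient received one treatment rather than the other. The authors give two main reasons, anatomy and surgeons' experience, and the score covers only the first. This goes beyond detail that an article leaves to an analysis plan, because the article states which classes of covariate the score uses and experience belongs to neither.

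The omission causes bias only if operators differ both in how often they cross limbs and in their patients' outcomes. The second condition is plausible. The primary outcome comprises inadequate distal seal, component separation or fabric tear, and limb occlusion, and these may depend partly on deployment. Operation time, radiation exposure and contrast dose may depend on the operator more directly.

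If more experienced operators cross more often, CL would look safer than it is and a false non-inferiority finding would become more likely. If they cross less often, CL would look worse and power would fall. The planned balance check can show balance only on variables that are recorded and examined.

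**Working it through.** **1. The texts side by side.** Determinants named in the Discussion: anatomy, surgeons' experience. Matching factors described as major: age, gender, aneurysm diameter. Propensity score: demographics, anatomy. Procedure details: operation time, radiation time, contrast dose. Experience appears in the first list and in none of the others.

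**2. The plan's sample size, to fix the scale.** Inputs from Sample size calculation: adverse limb events 11.5% (CL) and 7.9% (SL), margin 0.15, type I error 0.05, power 80%, ratio 4:11, dropout 20%. With unpooled variance and one-sided 0.05:

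n(SL) = (1.645 + 0.842)² × [0.079 × 0.921 + (11/4) × 0.115 × 0.885] / (0.15 − 0.036)² ≈ 168, and n(CL) = 168 × 4/11 = 61.1.

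Multiplying by 1.2 gives 201.6 and 73.3, which matches the stated 202 and 73. Expected events are 73 × 0.115 + 202 × 0.079 ≈ 8 + 16 = 24 among those enrolled, or 61 × 0.115 + 168 × 0.079 ≈ 7 + 13 = 20 among those evaluable.

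**3. Illustration with no true CL effect.** The operator figures are assumptions; the document gives none. Two operator groups of equal volume use CL in 40% and 13.3% of cases, which averages to the planned share of 4/15. Their event risks are 5% and 11%.

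- CL: (0.40 × 5 + 0.133 × 11) / 0.533 = 6.5%
- SL: (0.60 × 5 + 0.867 × 11) / 1.467 = 8.5%
- Spurious difference: about 2.0 points in favour of CL. With the two risks swapped, it is about 2.0 points against CL.

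The frequent-CL group performs 0.40/0.533 = 75% of CL cases and 0.60/1.467 = 41% of SL cases. The standardized difference is (0.75 − 0.41) / √[(0.75 × 0.25 + 0.41 × 0.59)/2] ≈ 0.74, against a target below 0.10. A check limited to demographic and anatomic variables would not look at it.

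**4. Consequences over an assumed range.** Bias = (difference between arms in the share of less experienced operators) × (operator effect on event risk). The test is an unweighted one-sided 0.05 comparison of risks with 61 and 168 evaluable patients. The standard error is √(0.115 × 0.885/61 + 0.079 × 0.921/168) = 0.0458 at the planning rates. It is √(0.229 × 0.771/61 + 0.079 × 0.921/168) = 0.0577 at the margin, where CL risk is 7.9% + 15% = 22.9%.

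Type I error = Φ(bias/0.0577 − 1.645). Power = Φ((0.114 − bias)/0.0458 − 1.645).

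| Imbalance × effect (points) | Bias (points) | Type I error if bias favours CL | Power if bias is against CL |
|---|---|---|---|
| none | 0 | 5.0% | 80.0% |
| 10 × 5 | 0.5 | 6.0% | 76.8% |
| 20 × 10 | 2.0 | 9.7% | 65.7% |
| 30 × 10 | 3.0 | 13.0% | 57.4% |
| 50 × 10 | 5.0 | 21.8% | 40.2% |
| 50 × 15 | 7.5 | 36.5% | 21.4% |

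The last rows need large operator differences in both respects.

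**The case against.** The case on the other side has real weight.

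- **The Discussion sentence is not the allocation rule.** It explains why randomized trials of this question are hard in general. This trial's rule starts from anatomy and turns to adaptive matching when either configuration is feasible, which is where preference would otherwise matter most. This narrows the concern. The operator still judges feasibility, and that judgement decides which patients reach the matching step.
- **Operator skill is restricted.** One centre, one device family, a standard protocol and an experienced surgeon all limit variation. They do not show that experienced surgeons are alike in CL use or results.
- **Articles condense.** The baseline list is open-ended, the matching factors are only the major ones, and case-report fields may sit in the full protocol. The operator can probably be retrieved from the operative record, so a reader who infers that the information is lost goes beyond the text. The stated make-up of the propensity score is unaffected by this.
- **The illustration is assumed.** It takes a threefold spread in CL use and a 2.2-fold spread in risk. The resulting 2.0 points is about one-seventh of the 15-point margin.
- **Events are few.** With about 20 to 24 expected, many operator terms would be unstable. A variable that predicts configuration but not outcome adds weight variance without removing bias.

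A reader might also infer that operator skill is confounded with configuration, or that every weighted result partly compares surgeons. The document supports neither: it gives no operator-level CL use or outcomes, and if a single surgeon did all the cases the concern would shrink, although the text speaks of surgeons in the plural.

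**Conclusion.** The point stands in limited form. Followed as written, the plan leaves out of the treatment model a determinant of treatment that its authors name, and no matching, weighting, stratification or subgroup statement makes up for it. Confounding by operator experience is possible but not shown. It would act mainly through the feasibility judgement, and its direction is unknown.

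The figure of about 2.0 points rests wholly on assumed operator spreads. It is small beside the margin but more than half the 3.6-point planning difference. The adjusted odds ratios, hazard ratios and intraoperative outcomes have no stated margin to absorb such a shift. This is a cheap improvement, not a flaw that invalidates the design.

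**What to change.** 1. In Data collection, record the primary operator in coded form, taken from the operative record.
2. In Statistical analysis, add one operator-experience term (for example high versus low EVAR volume) to the propensity model, or make that model a pre-specified sensitivity analysis.
3. Apply the existing standardized-difference target of below 0.10 to that term.
4. Report the CL share by operator, so that readers can see whether operators differ at all.

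The cost is one field and one model term. Patient treatment and the matching scheme stay as they are. The downside is somewhat more variable weights if some operators almost always use one configuration. Adding the operator as a matching factor, or operator terms with many levels, is not advised with 20 to 24 expected events.

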**FIGURE 1 F1:**
[figure not shown]
The procedure of screening, randomization and follow-up in the DANCER trial.

**TABLE 1 T1:** Inclusion and exclusion criteria for participants.

Inclusion	Exclusion
Patients are considered eligible if they meet all of the following criteria: 1. Men or non-pregnant women aged ≥ 18 years and with sufficient life expectancy to complete all the processes of the study. 2. Diagnosed with infrarenal abdominal aortic aneurysm (according to ICD I71.3 and I71.4) and indicated for surgical intervention. 3. Local anatomy of bilateral femoral and iliac arteries allows for guide wire passing. 4. Provide written informed consent and agree to participate in the study. 5. Placement of iliac endografts is required during the procedure.	Patients shall be excluded from the trial if they meet any of the following criteria: 1. Unable to tolerate contrast agents, antiplatelets or anticoagulants. 2. Recorded with previous primary repair for AAA, no matter EVAR or open surgical repair.

AAA, abdominal aortic aneurysm; EVAR, endovascular aneurysm repair.

We will recruit patients by putting up posters and advertising online to meet the expected enrollment. In addition, we provide fast-track follow-up for patients who are willing to participate in our study. Figure 2 shows the schedule of enrollment, interventions and assessments, following the template provided by SPIRIT (24).

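### The propensity score omits the Charlson index the trial collects, so weighted balance on comorbidity is neither targeted nor assured

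*Protocol article*

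**What the plan says.** The Statistical analysis section of the protocol article names two sources of covariates for the weighting model: "The propensity score to undergo CL or SL is estimated by logistic regression model based on demographic and anatomic information". It then sets a balance target, without listing the covariates to be checked: "Inverse probability of treatment weighting adjusted analyses are performed to achieve weighted balance with standardized differences < 0.10".

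The Data collection section names three classes, not two: "baseline data will be collected for both groups, including demographic characteristics, comorbidities and anatomical variables". It adds: "The comorbidity is evaluated by the Charlson Comorbidity Index to quantify its severity". The Quality control section gives staff special training in recording comorbidity.

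On how the configuration is chosen, Allocations of intervention says: "Based on the anatomic features of the aneurysm by intraoperative imaging, surgeons will determine whether to adopt CL or SL configuration". Where both configurations are feasible, assignment uses covariate-adaptive matching, and comorbidity is not among the covariates named: "The major matched covariates are as follows: age, gender and aneurysm diameter".

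**The concern.** The authors treat comorbidity as a class of its own, so it cannot be read into either of the two classes in the propensity sentence. That sentence is therefore a stated covariate rule that leaves out a prognostic variable the trial measures carefully.

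Surgeons choose the configuration unblinded, and the Discussion concedes considerable selection bias. The weights exist to deal with that. If comorbidity differs between the groups after weighting, a comparison of overall survival or major adverse cardiac events would carry part of that difference. The balance check would not reveal it unless comorbidity is among the variables checked, and the article does not say whether it is. Even without confounding, a chance imbalance in a prognostic variable costs precision that the weights could recover.

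**Working it through.** The plan gives no figure for comorbidity, so there is none to reproduce, and adding the index changes no stated figure. The inputs taken from the Sample size calculation section are the SL event risk of 7.9%, the CL risk of 11.5%, the margin of 0.15, and the enrolment of 73 CL and 202 SL. All other inputs below are assumptions.

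**1. Does omission imply imbalance?** Illustrative simulation, n = 400,000. Age and an anatomy score are independent standard normal variables; the Charlson score has unit variance and correlation 0.4 with age. The log-odds of CL are −1.2 + 0.3 × age + 0.8 × anatomy + g × Charlson, which gives about 26% CL. Entries are CL minus SL differences in mean Charlson score, in SD.

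| g (direct effect of comorbidity on choice) | Unweighted | Weighted, index omitted | Weighted, index included |
|---|---|---|---|
| 0 | 0.107 | −0.001 | −0.002 |
| 0.1 | 0.199 | 0.089 | 0.000 |
| 0.2 | 0.277 | 0.164 | 0.001 |
| 0.4 | 0.440 | 0.329 | 0.000 |

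With g = 0, weighting on age and anatomy removes the imbalance that came through age. With g = 0.2 or more, the residual exceeds the plan's own limit of 0.10. With the index in the model it is at most 0.002 in size.

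**2. Chance.** For a covariate independent of configuration, the standard error of the standardised difference is about √(1/73 + 1/202) = 0.137. Then P(|difference| > 0.10) = 2 × [1 − Φ(0.10/0.137)] = 0.46. With 58 and 161 patients, after 20% dropout, it is 0.51. This ignores the variance that weighting adds.

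**3. Size for the primary outcome.** Take a binary high-comorbidity indicator with residual prevalence pSL = 0.30 in SL and pCL in CL, a risk ratio RR for the event, and no true CL effect. The spurious risk ratio is

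[1 + pCL(RR − 1)] / [1 + pSL(RR − 1)],

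and the bias in points is 7.9 × (spurious ratio − 1).

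| pCL | RR = 1.5 | RR = 2 | RR = 3 |
|---|---|---|---|
| 0.30 | 1.000 (0.00) | 1.000 (0.00) | 1.000 (0.00) |
| 0.35 | 1.022 (0.17) | 1.038 (0.30) | 1.062 (0.49) |
| 0.40 | 1.043 (0.34) | 1.077 (0.61) | 1.125 (0.99) |
| 0.50 | 1.087 (0.69) | 1.154 (1.22) | 1.250 (1.98) |

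Worst case: (1 + 0.5 × 2)/(1 + 0.3 × 2) = 2.0/1.6 = 1.25, and 7.9 × 0.25 = 1.98 points. That is 1.98/15 = 13% of the margin. It is larger relative to the planning difference of 11.5 − 7.9 = 3.6 points, but the margin decides the trial. If CL patients had less comorbidity, the sign would reverse.

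**4. Size for survival.** The documents give no mortality figure. On an assumed 3-year mortality of 10%, the same spurious ratios of 1.00 to 1.25 give 0 to 2.5 points.

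**The case against.** The strongest reply is that the weighting model follows the stated drivers of choice. Allocation rests on anatomy seen during the procedure, and the Discussion justifies the lack of randomisation "as the performance of CL or SL is mainly based on anatomy and surgeons’ experience". No passage says that comorbidity influences CL versus SL, so a model built on demographics and anatomy is defensible, and the g = 0 row shows it can suffice. This stands as an answer to certain imbalance. It does not remove the point: the Discussion says mainly, not solely; chance imbalance remains; and a prognostic covariate is worth including in any case.

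A reader might infer that comorbidity will be unbalanced in every weighted comparison. The documents do not support that, because balance depends on whether comorbidity affects the choice once demographics and anatomy are accounted for.

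A reader might also infer that the weights serve every safety outcome. The article assigns short-term outcomes to multivariable logistic regression, and time-to-event outcomes to Cox regression as well as a marginal structural model. It lists no covariates for the regressions, so they may adjust for comorbidity. That would help those analyses but would not put the index in the weights.

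It is also tempting to add the admitting diagnosis code, since Table 1 admits patients "according to ICD I71.3 and I71.4". The documents do not say what the two codes distinguish, and a rare indicator could make the weights unstable with 73 CL patients. That addition is not supported.

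Finally, an article condenses, and the full covariate list may sit elsewhere. But this sentence names the classes used and leaves one of the three out.

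**Conclusion.** The point holds in a limited form. As written, the propensity model omits a baseline class that the trial collects, so weighted balance on comorbidity is neither targeted nor assured. Whether imbalance arises depends on surgeon behaviour that the documents do not describe, and on chance.

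The consequence is small for major adverse limb-graft events: 0 to 2.0 points against 15. This assumes 30% high comorbidity in SL, 30 to 50% in CL, and a risk ratio of 1 to 3; no passage links comorbidity to limb events at all. The consequence is potentially more important for weighted analyses of overall survival and major adverse cardiac events, where comorbidity plausibly predicts the outcome, but the documents give no figures from which to size it. It is worth correcting because the remedy is nearly free, not because the primary conclusion is in danger.

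**What to change.** Amend the propensity sentence so that the score is based on demographic, comorbidity (Charlson Comorbidity Index) and anatomic information. List the index in the standardised-difference check with the same 0.10 limit. If the authors prefer to leave it out, they should say why.

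The cost is one more term in the propensity model and one sentence of text. The data are already collected by trained staff, and neither sample size nor trial conduct changes.
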